### Sample size

Our proposed sample size (n=100) will enable us to detect the primary feasibility target of 90% protocol adherence with a 95% CI of 79 to 96%. The lower limit of this CI would be the minimum acceptable in the proposed large definitive trial. Furthermore, assuming a normal distribution for the time from randomization to RRT initiation in our trial and SD estimated from a previous trial (SD 4.96) [11], we estimate that our sample size will have >95% power to detect a difference of at least 24 hours in time to RRT initiation between the accelerated and standard arms. Considering secondary endpoints, our sample size will permit calculation of CIs of 43 to 57% for the enrollment of 50% of eligible patients and 89 to 98% for achievement of 95% followup to 90 days.

### Analysis

Analysis will be intention-to-treat. The primary feasibility analysis will evaluate the proportion (95% CI) of all randomized patients adhering to their allocated treatment. The secondary feasibility analyses will evaluate the proportion (95% CI) of all screened eligible participants who are enrolled, and the proportion (95% CI) of enrolled patients having vital status and RRT dependence at 90 days ascertained. The secondary safety analysis will evaluate differences in the incidence of adverse events between the accelerated and standard groups. Tertiary analyses of patient-centered and health-resource utilization outcomes between the groups will be performed, including mortality through day 90, need for RRT through day 90, a composite of major adverse kidney events (MAKE), duration of ICU stay, duration of hospitalization and hospital readmission through day 90.

Descriptive statistics, boxplots and histograms will be used to analyze individual baseline variables by accelerated or standard arms. Normally or near normally distributed, non-correlated variables will be reported as means with SD and compared using the appropriate Student’s *t*-test. Non-normally distributed, non-correlated continuous data will be reported as medians with IQRs and compared using the Mann Whitney *U*-test. Non-correlated categorical data, including the tertiary analyses such as mortality and need for RRT, renal recovery and hospital mortality, will be reported as proportions and compared using Fisher’s exact test. Normally distributed correlated data will be analyzed by repeated measures analysis of variance (ANOVA). Non-normally distributed correlated data will be analyzed by the Friedman test. Correlated categorical data will be analyzed by generalized estimating equations. A *P*-value <0.05 will be considered significant. All statistical tests will be two-sided.

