**Discussion:**

The optimal timing of renal replacement therapy initiation in patients with severe acute kidney injury remains uncertain, representing an important knowledge gap and a priority for high-quality research. This pilot trial is necessary to establish protocol feasibility, confirm the safety of participants and obtain estimated events rates for design of a large definitive trial.

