### Eligible, non-randomized patients

Eligible non-randomized patients will be those who meet all inclusion criteria but are not included in the trial for the following reasons:

1. A doubling of serum creatinine that has exceeded 48 hours at the time of screening (exclusion 7);

2. Clinician(s) belief that either immediate RRT is absolutely mandated (exclusion 8) or deferral of RRT initiation (exclusion 9) is absolutely mandated; or

3. Refusal of consent or inability to obtain consent within 12 hours of patient meeting eligibility criteria (exclusion 10).

We will document reasons leading to non-inclusion of these otherwise eligible patients. For these patients, we will collect data on kidney function at baseline and at the time of eligibility, severity of illness at the time of eligibility, receipt of RRT in hospital and need for RRT at hospital discharge, and vital status at ICU and hospital discharge. The collection of these data will enable comparisons with randomized patients to assess threats to the generalizability of the trial results.

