### Randomization process

Participants will be randomly allocated in a ratio of 1:1, stratified by study center using variable block sizes undisclosed to site study personnel, to accelerated or standard initiation of RRT. The study statistician at the methods centre (Applied Health Research Centre (AHRC), St. Michael’s Hospital, Toronto, Canada) will generate the random allocation sequence using computer software. Randomization information for each site will be contained in locally held sequentially numbered, opaque, sealed envelopes. Envelopes are to be opened in numeric sequence.

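### The tertiary mortality and kidney-outcome comparisons are fixed as unadjusted Fisher's exact tests, which are valid but give up a modest amount of precision that one baseline severity score could recover

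*Protocol article*

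**What the plan says.** Under Analysis, the between-arm comparisons of mortality, need for RRT, the composite of major adverse kidney events and resource use are labelled tertiary. The method for the categorical ones is fixed there: "Non-correlated categorical data, including the tertiary analyses such as mortality and need for RRT, renal recovery and hospital mortality, will be reported as proportions", and these "will be reported as proportions and compared using Fisher’s exact test". No baseline variable enters. The composite kidney outcome is not named in that sentence, but as a non-correlated categorical outcome it falls under the same rule. The threshold is "A *P*-value <0.05 will be considered significant", and "All statistical tests will be two-sided". The same section attaches 95% CIs to the feasibility proportions; for between-arm outcomes it names tests.

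Under Randomization process: "Participants will be randomly allocated in a ratio of 1:1, stratified by study center using variable block sizes undisclosed to site study personnel". Severity is not a stratification factor.

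Under Eligible, non-randomized patients, the data to be collected include "severity of illness at the time of eligibility" and kidney function, for comparison with randomized patients. That comparison is possible only if randomized patients have the same data. Their recording is therefore implied, not stated, and no baseline score is named.

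The abstract's Discussion says that the pilot is to establish feasibility, confirm safety and "obtain estimated events rates for design of a large definitive trial".

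**The concern.** With about 50 patients per arm and no stratification on severity, the arms will often differ somewhat in baseline prognosis by chance. A crude comparison leaves that difference in the realized risk difference. A model with a prognostic baseline score removes most of it and so narrows the interval. The score would be measured before allocation, so adjusting for it is safe. The plan names the crude test for these outcomes, so the choice is made in the article and not left open. At stake is the precision of the tertiary estimates. The primary adherence analysis and the feasibility targets are untouched.

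**Working it through.** **The plan's own figure.** None exists for this point: the Sample size section sizes no mortality or kidney-outcome comparison.

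**Inputs.** From the article: n = 100, allocated 1:1, so about 50 per arm; Fisher's exact test; two-sided 0.05. Assumed: mortality of 40 to 60% (Background gives only a case-fatality rate, commonly above 60%, in patients who receive RRT) and the prognostic strength of the severity score, for which the article gives no value.

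**Step 1: precision of the crude difference.** SE = sqrt(2p(1−p)/50).
- p = 0.5: SE = 0.100; half-width 1.96 × 0.100 = 19.6 points.
- p = 0.4 or 0.6: SE = 0.098; half-width 19.2 points.

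**Step 2: size of chance imbalance.** The standardized difference in severity between arms has SE sqrt(2/50) = 0.20. The chance that it exceeds 0.3 in either direction is 2 × P(Z > 0.3/0.20) = 2 × P(Z > 1.5) = 13.4%.

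**Step 3: what such an imbalance does.** With an assumed odds ratio of 2 per SD and 50% mortality, an imbalance of 0.3 moves the realized crude difference by about 0.3 × ln 2 × 0.25 = 0.052, or 5 points. That is about a quarter of the half-width in Step 1 (5.2/19.6 = 0.27).

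**Step 4: gain from adjustment.** Trials with 50 per arm, 50% mortality and no treatment effect were simulated. The crude risk difference was compared with one standardized from a logistic model on arm and one severity score.

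| Assumed odds ratio per SD | Simulated trials | SD crude | SD adjusted | Fall in SD | (crude/adjusted)² |
|---|---|---|---|---|---|
| 1.5 | 1,500 | 0.0988 | 0.0982 | 0.6% | 1.01 |
| 1.65 (AUC 0.64) | 4,000 | 0.100 | 0.098 | 2.0% | 1.04 |
| 2 | 1,500 | 0.1001 | 0.0956 | 4.5% | 1.10 |
| 2.23 (AUC 0.70) | 4,000 | 0.102 | 0.096 | 5.9% | 1.13 |
| 2.72 (AUC 0.74) | 4,000 | 0.101 | 0.091 | 9.9% | 1.23 |
| 3 | 1,500 | 0.1001 | 0.0901 | 10.0% | 1.23 |
| 3.67 (AUC 0.79) | 4,000 | 0.101 | 0.088 | 12.9% | 1.32 |

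The last column is the equivalent ratio of sample sizes. In the 4,000-trial runs, the SD of the shift caused by severity imbalance was 0.022, 0.036, 0.043 and 0.050. Removing it reproduces the adjusted SD: for AUC 0.70, sqrt(0.102² − 0.036²) = 0.095, against 0.096 simulated; for AUC 0.79, sqrt(0.101² − 0.050²) = 0.088, as simulated. At the strongest setting the half-width falls from 1.96 × 0.101 = 19.8 points to 1.96 × 0.088 = 17.2 points.

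**Step 5: validity of the crude method.** In the 4,000-trial runs with a prognostic score and no true effect, the mean difference was 0.00 both crude and adjusted. Fisher's test rejected in 3.5 to 3.8% of trials, and the adjusted Wald test of the arm coefficient in 4.8 to 5.2%. Coverage of the standardized interval itself was not simulated.

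**Step 6: power is not the argument.** With true rates of 50% and 30%, Fisher's test rejected in 45 to 48% of trials and the adjusted test in 55 to 63%. With a score unrelated to outcome the figures were already 46% and 54%, so much of that gap is Fisher's conservatism.

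**The case against.** The strongest reply is that nothing here is an error. Randomization makes the crude difference unbiased, and chance imbalance is part of the sampling error that the test allows for. The comparisons are tertiary in a feasibility pilot, and even the adjusted interval is too wide to guide an effect size: power for a 7.5-point difference, the target of the large trial cited in Background, is about 11 to 12%. The gain depends on a prognostic strength that the article does not give. Supplementary models may also sit in an analysis plan that is not shown. All of this stands, except that the last part only limits the point: the article names the method for these outcomes, so improving that stated choice is fair comment.

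A reader might infer that the between-arm mortality and kidney estimates are meant to feed the definitive trial, so that imbalance would distort its design. The documents do not support this. They carry forward event rates, feasibility and safety, and no treatment effect. A pooled event rate does not depend on balance between the arms; its half-width is 1.96 × sqrt(0.25/100) = 9.8 points at 50% mortality.

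A reader might also take severity to be the main driver of death in this population, or its recording in randomized patients to be stated. The article says neither.

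**Conclusion.** A minor point of efficiency, not of validity. The unadjusted tests are correct, but they leave unused a baseline measure that the trial very probably holds. Adjustment would lower the SD of the risk difference by about 1 to 13%, equivalent to roughly 1 to 32% more patients, against a crude half-width of about 19 to 20 points. This rests on 50 patients per arm, mortality near 50%, an assumed odds ratio of 1.5 to 3.67 per SD of severity, and a score that is complete in randomized patients. If the score predicts outcome weakly, the gain is close to nil. No conclusion on adherence, enrollment or follow-up changes.

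**What to change.** For day-90 mortality and the composite kidney outcome, prespecify a risk difference with 95% CI, standardized from a logistic model with arm and one severity score measured at eligibility. Report it beside the crude proportions. Name the score in advance, confirm that it is collected for every randomized patient, and state how a missing value will be handled. The article names no suitable score: the only one it mentions, the cardiovascular SOFA component, is used when RRT starts, to guide modality.

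The cost is one small model per outcome and a line in the results table. The drawback is dependence on that score being complete.

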## Background

Acute kidney injury (AKI) is a common complication in critically ill patients. Among those with severe AKI, 50 to 70% will receive renal replacement therapy (RRT) [1]. RRT increases the complexity and costs of care and is associated with death, with case-fatality rates commonly exceeding 60% [1,2], and dialysis dependence among survivors [2-4].

Methods of providing RRT to patients in the ICU vary widely, reflecting uncertainty surrounding many aspects of this therapy [5,6]. It is generally understood that life-threatening AKI complications, such as severe hyperkalemia, profound acidosis and fluid overload resulting in respiratory failure, are absolute indications for RRT. However, outside of these indications, the optimal time to start RRT in critically ill patients with severe AKI remains unknown. Early initiation of RRT has the intuitive appeal of avoiding life-threatening AKI complications; however, RRT is not without complications and costs [7,8], and in the setting of chronic dialysis for end-stage renal disease, no evidence of benefit was found with earlier start times [9].

We recently performed a systematic review of the effect of RRT timing on mortality in adult critically ill patients, and included 15 studies published between 1999 and 2010 [10]. In a pooled analysis limited by low methodological quality of the included studies and important statistical heterogeneity, early (versus later) initiation of RRT was associated with a significantly reduced odds of death (odds ratio 0.45, 95% CI 0.28, 0.72). The largest published randomized controlled trial (RCT) (n=106) of RRT timing found no difference in mortality; however, it was underpowered to detect a clinically implausible absolute difference in mortality of less than 40% [11]. For comparison, the large multi-cente rtrial, Randomized Evaluation of Normal versus Augmented Level Renal Replacement Therapy (RENAL),enrolled 1,508 critically ill patients with severe AKI and was powered to detect a minimal difference in 90-day mortality of 7.5% [12].

Given the limitations of published studies, a large and methodologically rigorous RCT is needed to evaluate the impact on survival and renal recovery of earlier versus current usual criteria for RRT initiation in critically ill adults with severe AKI. This question has also been identified as a top research priority by the Acute Kidney Injury Network [13] and endorsed by intensivists and nephrologists [14].

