### Setting

The setting is the ICU at 12 academic hospitals across Canada. Site investigators are listed in Additional file 1.

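### Allocation is stratified by 12 centres, but the between-arm tests named for safety and tertiary outcomes have no centre term; they are conservative and lose some power

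*Protocol article*

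**What the plan says.** **Design.** Under Setting: "The setting is the ICU at 12 academic hospitals across Canada". Under Randomization process: "Participants will be randomly allocated in a ratio of 1:1, stratified by study center using variable block sizes undisclosed to site study personnel".

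**Analysis.** The Analysis section assigns tests by type of data:

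- Fisher's exact test for categorical data treated as non-correlated: "including the tertiary analyses such as mortality and need for RRT, renal recovery and hospital mortality, will be reported as proportions and compared using" that test.
- Non-correlated continuous data: Student's t-test if near normal, otherwise Mann-Whitney.
- Correlated data: repeated-measures ANOVA if normal. Otherwise, "Non-normally distributed correlated data will be analyzed by the Friedman test". Correlated categorical data go to generalized estimating equations (GEE).

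All tests are two-sided at 0.05. The article mentions centre only for the allocation; no analysis method carries it. The between-arm comparisons are the secondary safety analysis (incidence of adverse events) and the tertiary outcomes. The primary analysis (adherence) and the two feasibility analyses (enrolment, 90-day ascertainment) are single proportions with 95% CIs and involve no test between arms.

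**The concern.** When allocation is balanced within centres and centres differ in risk, the balance removes the between-centre part of the variation from the arm difference. A test that ignores centre still counts that part as noise. Its p-values are then too large on average and its power is lower than the design allows.

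What is at stake is limited but real. The pilot is meant to confirm participant safety, and the comparison of adverse-event incidence is a secondary analysis. A needlessly conservative test makes a harm signal easier to miss among 100 patients. The same applies to mortality and need for RRT by arm, which readers will look at before a definitive trial.

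The Friedman test raises a smaller point of the same kind. It ranks values within each patient, so it cannot show a difference between arms.

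**Working it through.** No figure in the article rests on these tests, so there is nothing to reproduce. The check compares the named test with one that follows the randomization.

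**Inputs from the article.** 12 centres, 1:1 allocation stratified by centre, N = 100 (100/12, about 8 per centre), two-sided 0.05.

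**Assumed, not in the article.** Centre effects normal on the logit scale with SD 0, 0.5 or 1.0; control risk 50% or 60%; an absolute reduction of 25 points at a centre of average risk.

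**Why ignoring centre is conservative.** With risk p_k in centre k and mean risk p̄, the pooled test uses p̄(1 − p̄), which equals mean[p_k(1 − p_k)] + Var(p_k). Balanced allocation within centre removes Var(p_k) from the true variance of the arm difference, but the pooled test keeps it.

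**Why the estimate hardly moves.** The Mantel-Haenszel risk difference is Σ w_k d_k / Σ w_k, with d_k the risk difference in centre k and w_k = n1_k n0_k / n_k. If n1_k = n0_k = n_k/2, then w_k = n_k/4 and d_k = (x1_k − x0_k)/(n_k/2). The ratio becomes (X1 − X0)/(N/2), the crude difference. Stratifying changes the standard error and p-value, not the reported proportions.

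**Simulation.** Eight centres of 8 and four of 9 (64 + 36 = 100), split evenly within centre and 4/5 at random where odd; 10,000 trials per setting. Monte Carlo standard error is about 0.2 points for size, √(0.05 × 0.95/10,000), and 0.5 for power. An unstratified chi-square is included to separate Fisher's own conservatism from the effect of ignoring centre.

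| Control risk | Centre SD | Type I error: Fisher / chi-square / stratified | Power: Fisher / chi-square / stratified |
|---|---|---|---|
| 50% | 0 | 4.0 / 5.7 / 4.9% | 69.6 / 74.9 / 74.1% |
| 50% | 0.5 | 4.2 / 5.7 / 5.6% | 65.8 / 71.9 / 72.1% |
| 50% | 1.0 | 2.8 / 3.9 / 4.9% | 55.1 / 61.5 / 66.7% |
| 60% | 0 | 3.9 / 5.7 / 5.4% | 67.9 / 73.0 / 70.5% |
| 60% | 0.5 | 3.1 / 4.4 / 4.5% | 63.8 / 69.3 / 68.9% |
| 60% | 1.0 | 2.3 / 3.7 / 5.2% | 52.0 / 58.3 / 63.0% |

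Gain of the stratified test over Fisher at SD 0, 0.5 and 1.0: 4.6, 6.3 and 11.6 points at 50% (for example 66.7 − 55.1 = 11.6), and 2.7, 5.1 and 11.0 points at 60%. Three other sets of runs, with somewhat different risks and effects, agree:

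- about 2, 4 and 10 points;
- 72.3 − 68.6 = 3.7, 71.7 − 65.9 = 5.8 and 67.9 − 56.4 = 11.5 points;
- 84.0 − 79.3 = 4.7, 81.8 − 75.7 = 6.1 and 76.3 − 64.4 = 11.9 points.

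**Splitting the gain.** Moving from Fisher to an unstratified chi-square already gives about 5 to 6 points in every row. Moving on to the stratified test adds nothing material at SD 0 or 0.5 (between −2.4 and +0.3 points). At SD 1.0 it adds 66.7 − 61.5 = 5.2 and 63.0 − 58.3 = 4.7 points. Part of the chi-square's advantage at SD 0 comes from a size slightly above 5%. As a cross-check, the exact size of Fisher's test for 50 against 50 at 60% risk, with no centre effect at all, is 3.2%.

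**Friedman.** With 100 simulated patients at 5 time points, adding 10 units to every value in one arm left the Friedman statistic unchanged (2.584, p = 0.63 both times). A Mann-Whitney test on patient means gave p = 7 × 10⁻¹⁸. Ranking within patients removes any constant arm difference.

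**The case against.** The strongest reply is that little depends on this. The primary and feasibility results are single proportions. The affected comparisons are secondary safety and tertiary outcomes in a pilot with about 8 patients per centre. The direction is conservative, so no false positive is created. The reported proportions stay as they are, much of the shortfall is Fisher's own, and the centre SDs are assumed. All of this stands and limits the size of the point. It does not remove the mismatch between an allocation that is "stratified by study center using variable block sizes undisclosed to site study personnel" and tests that ignore it.

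Three stronger readings are tempting and not supported:

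- **That the Friedman test is assigned to compare the arms.** The section names no correlated outcome and no time points, and does not say that this test compares arms. It is a loosely placed method, not a stated wrong comparison.
- **That stays cut short by death are scored as good results.** The article lists "duration of ICU stay, duration of hospitalization and hospital readmission through day 90" among the tertiary outcomes and gives no rule for deaths. How to treat such stays is a choice of estimand that an article may leave to the full protocol or analysis plan, and as a measure of resource use a stay ended by death is in fact shorter. The Background figure, "case-fatality rates commonly exceeding 60" per cent, concerns patients who receive RRT. It is not an expected mortality for this trial, whose standard arm includes patients who may never start RRT.
- **That the whole power gap comes from ignoring centre.** The unstratified chi-square results show otherwise.

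**Conclusion.** The point holds in a limited form. The protocol article fixes unstratified tests for the secondary safety and tertiary between-arm comparisons although allocation is stratified by 12 centres. Over assumed centre SDs of 0 to 1.0, Fisher's type I error is about 2 to 4%, and a centre-stratified Mantel-Haenszel test gains roughly 2 to 12 points of power. Ignoring centre accounts for next to none of that gain at SD 0.5 or below and for about 5 points at SD 1.0; the rest is Fisher's conservatism. The power figures also rest on an assumed 25-point effect, which the article does not claim to be able to detect. The simulation covers binary outcomes only. For the t-test and Mann-Whitney the same reasoning gives the direction, but no size was computed. The primary adherence result and the feasibility proportions are untouched. This is an inexpensive improvement, not a threat to the pilot's conclusions.

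**What to change.** In the Analysis section, or in the statistical analysis plan if one takes precedence:

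1. Compare binary safety and tertiary outcomes with a centre-stratified Mantel-Haenszel risk difference and 95% CI.
2. Compare continuous outcomes with a van Elteren test stratified by centre, or a regression with a centre term.
3. State in advance how very small centres are merged, since a centre with patients in one arm only contributes nothing to a stratified comparison.
4. If any non-normal repeated measure is to be compared between arms, replace the Friedman test with a mixed model or GEE with arm-by-time terms. If none is planned, delete the sentence.

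The cost is analysis wording and programming. No new data, patients or visits are needed.

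### A single P<0.05 significance rule covers the safety comparison and the tertiary patient outcomes of a 100-patient feasibility pilot, with no exploratory status and too little power for either answer to mean much

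*Protocol article*

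**What the plan says.** All of this stands in the Analysis section of the protocol article unless noted.

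- **Feasibility outcomes.** Adherence (primary), enrolment and 90-day ascertainment (secondary) are each a proportion with a 95% CI. No between-arm test is planned for them.
- **Safety.** "The secondary safety analysis will evaluate differences in the incidence of adverse events between the accelerated and standard groups".
- **Patient outcomes.** "Tertiary analyses of patient-centered and health-resource utilization outcomes between the groups will be performed, including mortality through day 90, need for RRT through day 90". The list continues with MAKE, ICU stay, hospital stay and readmission, six in all. The next paragraph, on tests for categorical data, also mentions renal recovery and hospital mortality, which makes eight.
- **Baseline.** "Descriptive statistics, boxplots and histograms will be used to analyze individual baseline variables by accelerated or standard arms". The sentences that follow assign tests by data type and do not say whether baseline variables are included.
- **Decision rule.** "A *P*-value <0.05 will be considered significant. All statistical tests will be two-sided".
- **Timing of RRT.** The Sample size section claims more than 95% power for a 24-hour between-arm difference in time to RRT initiation. The last paragraph of the Background makes separation in timing an aim of the pilot.
- **Purpose.** The Discussion paragraph of the abstract presents the pilot as preparation for a later study: "This pilot trial is necessary to establish protocol feasibility, confirm the safety of participants and obtain estimated events rates for design of a large definitive".

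**The concern.** The rule gives the same status to a 90-day mortality test, a length-of-stay test and an adverse event test as to the one between-arm comparison for which the trial claims power. Two misreadings follow.

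First, a chance P below 0.05 on mortality, MAKE or another tertiary outcome would, by the plan's own rule, be called significant. The Background criticises an earlier trial of 106 patients on this question as underpowered for mortality, and contrasts it with a 1,508-patient trial powered for 7.5 percentage points. The same reasoning applies to a mortality test in 100 patients.

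Second, the pilot is meant to confirm safety, and the safety analysis is a between-arm difference judged by the same threshold. A real excess of adverse events would often miss it and could be taken as reassurance.

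Both readings could colour how the pilot informs the definitive trial.

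**Working it through.** **Inputs from the protocol.** n = 100, allocated 1:1, taken as 50 per arm; two-sided 0.05; Fisher's exact test for categorical outcomes; Mann-Whitney for non-normal durations; six tertiary outcomes, or eight with renal recovery and hospital mortality; 16 adverse event types in Table 2 (8 RRT-related, 8 catheter-related).

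**Assumed, because the protocol gives no figures.** Day-90 mortality 40%, RRT at day 90 15%, MAKE 50%, readmission 20%, hospital mortality 35%, renal recovery 40%; latent correlation between outcomes 0, 0.5 or 0.8.

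**1. The plan's own power figure.** With SD 4.96 read as hours, SE = 4.96 × √(2/50) = 0.992 h. Then 24/0.992 = 24.2, and power Φ(24.2 − 1.96) is about 100%, consistent with the stated >95%. The unit of the SD is not given. Read as days (119 h), SE = 23.8 h and power = Φ(1.01 − 1.96), about 17%. The stated figure is reproduced on the hours reading. It needs a significance level, and the sentence at issue is the only place that supplies one.

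**2. Simple bound on false positives.** For k independent tests at exactly 0.05, the chance of at least one is 1 − 0.95^k: 26.5% for k = 6 and 33.7% for k = 8.

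**3. Allowing for Fisher's test.** At 50 per arm its exact size is 0.0239 at a 15% event rate, 0.0282 at 20%, 0.0304 at 35%, 0.0321 at 40% and 0.0352 at 50%. The two durations are taken at 0.05.

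- Six outcomes, independent: 1 − (0.9679 × 0.9761 × 0.9648 × 0.9718 × 0.95²) = 0.20.
- Eight outcomes: 1 − (0.7994 × 0.9696 × 0.9679) = 0.25.

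**4. Allowing for correlation.** Simulation under no effect on any outcome (one-factor latent normal model, 20,000 replicates):

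| Tests | Correlation 0 | 0.5 | 0.8 |
|---|---|---|---|
| Six tertiary | 0.200 | 0.175 | 0.143 |
| Eight | 0.251 | 0.214 | 0.167 |

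The zero-correlation column agrees with step 3. If all 16 adverse event types and death to day 14 were also tested, the chance would be about 0.24 to 0.48, depending on the correlation and on the adverse event rates assumed (2 to 30%).

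**5. Power of the same tests** (exact, two-sided Fisher, 50 per arm):

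- Adverse event 10% against 20% (assumed): about 19%.
- Adverse event 5% against 10% (assumed): about 6%.
- Mortality 60% against 52.5%: about 9%. The 60% is an assumption guided by the case-fatality quoted in the Background; 7.5 points is the difference that the larger trial cited there was powered for.

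**6. What an interval would show.** Suppose 20% and 10% are observed. The difference is 10 points, SE = √(0.2 × 0.8/50 + 0.1 × 0.9/50) = 0.0707, and the 95% CI is about −4 to 24 points. That result is not significant, yet plainly compatible with substantial harm.

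**The case against.** The case on the other side is strong in several places.

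- **The outcomes are ranked.** Adherence is primary, feasibility and safety secondary, patient outcomes tertiary. A reader might infer that the plan has no hierarchy at all; it does. What is absent is a testing order or a statement that the lower ranks are exploratory.
- **The rule has a legitimate use.** A reader might infer that it governs only safety, tertiary and baseline comparisons and could be deleted. The Sample size section powers a between-arm comparison of time to RRT initiation, and deletion would leave that without a significance level. This stands, and it shapes the fix.
- **Testing each adverse event type is not stated.** The plan speaks only of differences in incidence. The 24 to 48% range is therefore conditional and is not the headline. The no-effect model also suits safety poorly: Table 2 lists events of RRT and its catheter, to which the accelerated arm is assigned by design, so a real difference is plausible. For safety the problem is low power.
- **Baseline testing is not explicit.** The only sentence naming baseline variables is descriptive. Testing them is a fair inference from the sentences that follow, but no more.
- **Unadjusted tertiary tests are usual in a pilot, and multiplicity detail is commonly left to a fuller document.** This is right as far as it goes, and the lack of an adjustment is not the point here. The point is what the article does fix: a rule that calls these results significant.
- **No tertiary P value is a go/no-go criterion, and a DSMB monitors adverse events.** Both are true, and they limit the harm. They do not change how the rule would have the final comparisons described.

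**Conclusion.** The point holds in a limited form. One two-sided 0.05 rule is attached to a safety comparison and six to eight tertiary outcomes, in a pilot whose stated aims are feasibility, separation in RRT timing, safety and event rates. The chance of at least one false significant tertiary result is about 14 to 20% for six outcomes and 17 to 25% for eight. These figures rest on 50 per arm, no true effect, and assumed event rates and correlations. Power of about 19% for a doubling of an adverse event from 10% to 20% (also assumed) means that non-significance cannot confirm safety.

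The adherence conclusion does not depend on any of these tests. This is a minor improvement to the wording.

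**What to change.** Make three changes in the Analysis section:

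1. Keep the two-sided 0.05 level, and tie it by name to the comparison of time to RRT initiation described under Sample size.
2. State that all between-arm comparisons of adverse events and tertiary outcomes are exploratory. Report them as risk differences or differences in medians with 95% CIs, make no claim of significance from them, and do not take a non-significant difference as evidence of safety.
3. State that baseline variables are summarised by arm without tests.

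This extends to the lower-ranked outcomes the estimation approach already used for feasibility. It needs no new data or patients. The cost is that the sponsor gives up calling a tertiary result significant.
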